## Background and rationale for study

The ACT HIV clinical trial is a randomised double-blind placebo-controlled trial of adjunctive dexamethasone for the treatment of tuberculous meningitis (TBM) in HIV-positive adults. TBM is the most severe form of tuberculosis, with mortality approaching 50% in people living with HIV
^
2–
5
^ despite the best available appropriate anti-TB chemotherapy.

TBM develops when
*Mycobacterium tuberculosis*, initially acquired via the respiratory route, disseminates via the blood to form a secondary focus in the brain. Rupture of this secondary focus into the subarachnoid space results in TBM, with the consequent host inflammatory response being important for bacterial killing, but also responsible for the pathological complications and often-fatal consequences of the infection.

Adjunctive anti-inflammatory corticosteroid therapy, which may control excessive host inflammation, has long been considered to have a role in TBM treatment
^
6
^. In 2004, a landmark clinical trial in Vietnam demonstrated that a 6–8 week (duration dependent on Modified Research Council [MRC] TBM severity grade) tapering course of dexamethasone reduced mortality in adults and adolescents with TBM
^
4
^. In this study, only 98/545 (18.0%) individuals were HIV positive, which was too small to determine if dexamethasone benefited this important sub-group of patients. No other trials have been published since 2004 that examine whether corticosteroids improve outcomes from TBM in HIV-positive adults.

How dexamethasone might confer its clinical benefit on those with TBM remains uncertain. A recent study of cerebrospinal fluid (CSF) cytokines in TBM suggested that HIV-positive individuals have higher cytokine concentrations than HIV-negative individuals
^
7
^. Whether adjunctive dexamethasone is more or less likely to be beneficial in HIV-positive individuals with TBM is not known. There are an estimated 100,000 cases of TBM globally each year
^
8
^, many associated with HIV. Clinical trial data are required to provide an evidence base for adjunctive dexamethasone in HIV-positive individuals with TBM, and to guide clinical practice.

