### Adverse events until 12 months

Serious adverse events (SAE) are defined in the study protocol
^
1
^. SAE will be sub-grouped into categories. SAE will be grouped and graded as per Common Terminology Criteria for Adverse Events (CTCAE)
^
14
^.

The number of patients with any serious adverse event will be summarised and compared between the two treatment arms based on the chi-squared test, or Fisher’s exact test in case the expected count under the null hypothesis in at least one of the cells is smaller than one
^
15
^. Specific adverse events will be summarised, but not formally compared. The total number of serious adverse event episodes per patient will also be summarised and informally compared based on a quasi-Poisson regression model with treatment as the only covariate.

The following subgroups of adverse events will also be separately summarised: clinical grade 3&4 adverse events; serious adverse events possibly, probably, or definitely related to the study drug; adverse events leading to TB treatment or ARV interruptions. Grade 3&4 laboratory abnormalities will be summarised in the same way as clinical adverse events. Adverse events will be shown as per
Table 6–
Table10.

**Table 6a. T6:** Summary of serious adverse events.

Characteristic	Dexamethasone (N=XX)		Placebo (N=XX)		Comparison (p-value)
	N.pt	N.ae	N.pt	N.ae	
Any selected serious adverse event	XX (XX%)	XX	XX (XX%)	XX	X.XX
Serious adverse events of all types	XX (XX%)	XX	XX (XX%)	XX	X.XX

N.pt = the number of patients with at least one serious adverse event (% of all patients receiving the same intervention) N.ae = the total number of episodes of that particular serious adverse event

**Table 6b. T6b:** Summary of serious adverse events, shown by reasons for which they were considered serious, not shown by study arm.

	Causes death (N=XX)	Life threatening event * (N=XX)	Hospitalisation of prolongation of hospitalisation (N=XX)	Persistent or significant disability/ incapacity ** (N=XX)	Congenital anomaly/ birth defect (N=XX)	Important medical event which may jeopardise the patient and/or require intervention (N=XX)
	n Summary statistic	n Summary statistic	n Summary statistic	n Summary statistic	n Summary statistic	n Summary statistic
Name of event	XX (XX%)	XX (XX%)	XX (XX%)	XX (XX%)	XX (XX%)	XX (XX%)

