* Subjects were at immediate risk of death at the time of the event; it does not refer to an event which hypothetically might have caused death if it were more severe ** A substantial disruption of a person's ability to conduct normal life functions N is the number of all patients, n is the number of patients with a non-missing value Summary statistic is absolute count (%) for categorical variable(s).

**Table 7. T7:** Summary of serious adverse events possibly, probably, or definitely related to the study drug.

Characteristic	Dexamethasone (N=XX)		Placebo (N=XX)		Comparison (p-value)
	N.pt	N.ae	N.pt	N.ae	
Any selected serious adverse event possibly, probably, or definitely related to the study drug	XX (XX%)	XX	XX (XX%)	XX	X.XX
Serious adverse events of all types possibly, probably, or definitely related to the study drug	XX (XX%)	XX	XX (XX%)	XX	X.XX

N.pt = the number of patients with at least one serious adverse event (% of all patients receiving the same intervention) N.ae = the total number of episodes of that particular serious adverse event

**Table 8. T8:** Summary of clinical grade 3&4 adverse events.

Characteristic	Dexamethasone (N=XX)		Placebo (N=XX)		Comparison (p-value)
	N.pt	N.ae	N.pt	N.ae	
Any selected clinical grade 3&4 adverse event	XX (XX%)	XX	XX (XX%)	XX	X.XX
Clinical grade 3 adverse events of all types	XX (XX%)	XX	XX (XX%)	XX	X.XX
Clinical grade 4 adverse events of all types	XX (XX%)	XX	XX (XX%)	XX	X.XX
Clinical grade 3&4 adverse events of all types	XX (XX%)	XX	XX (XX%)	XX	X.XX

N.pt = the number of patients with at least one adverse event (% of all patients receiving the same intervention) N.ae = the total number of episodes of that particular adverse event The ‘clinical grade 3&4 adverse events of all types’ grouping will include only the group of adverse events that cannot be separated into grades 3 or 4 (recorded as ‘grade 3 or 4’ at the beginning of the trial). These events will not also be represented in the above ‘grade 3’ and ‘grade 4’ rows.

**Table 9. T9:** Summary of adverse events leading to TB treatment or antiretroviral (ARV) interruptions.

Characteristic	Dexamethasone (N=XX)		Placebo (N=XX)		Comparison (p-value)
	N.pt	N.ae	N.pt	N.ae	
Any selected adverse event leading to TB treatment or antiretroviral interruptions	XX (XX%)	XX	XX (XX%)	XX	X.XX
Adverse events of all types leading to TB treatment or antiretroviral interruptions	XX (XX%)	XX	XX (XX%)	XX	X.XX

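### Table 8 has no row for fatal events and Table 6b pools the arms, so no planned table shows fatal adverse events by arm

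*SAP article*

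**What the plan says.** All of this is in the SAP article, section Adverse events until 12 months, unless another section is named.

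- **Grading.** SAEs are to be grouped and graded by CTCAE. The SAP does not reproduce the grades, and it has no rule on how an event that ends in death is graded.
- **Severity summary.** "The following subgroups of adverse events will also be separately summarised: clinical grade 3&4 adverse events". Table 8 sets this out by arm with a p-value column. Its highest single-grade row is "Clinical grade 4 adverse events of all types". The combined grade 3&4 row below it is not a total. Its footnote limits it to events recorded early in the trial that cannot be split into 3 or 4, and adds: "These events will not also be represented in the above ‘grade 3’ and ‘grade 4’ rows".
- **Fatal events.** Table 6b has a column for events that cause death, but its title reads: "Summary of serious adverse events, shown by reasons for which they were considered serious, not shown by study arm".
- **SAEs by arm.** "The number of patients with any serious adverse event will be summarised and compared between the two treatment arms based on the chi-squared test", with Fisher's exact test as the fallback. Table 6a reports this, and Table 7 does the same for SAEs judged related to study drug. Neither has a grade limit.
- **Mortality.** All-cause death to 12 months is the primary endpoint and Table 3 gives it by arm. The background section describes the disease "with mortality approaching 50% in people living with HIV".

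**The concern.** Table 8 is the only clinical adverse event table organised by severity. If a fatal event is graded above 4, it enters none of the table's rows. A patient who survives a severe infection or bleed is then counted, while one who dies of it is counted only if there was also a separate non-fatal grade 3 or 4 event. The comparison is in effect restricted to non-fatal events, and death is common enough here for that restriction to matter.

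The distortion can go either way. A treatment that prevents deaths leaves more patients whose severe events are counted, and so can look more toxic. A treatment that causes fatal complications moves patients out of the table, and so can look safer. Which adverse events were fatal, and in which arm, is a natural safety question for a corticosteroid in people with HIV. The planned tables do not answer it directly.

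**Working it through.** The SAP states no figure on this point, so there is nothing to reproduce. I read the tables side by side and then worked through illustrative counts.

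**Where a fatal adverse event is counted**

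| Table | By arm? | Fatal events included? | Fatal events distinguishable? |
|---|---|---|---|
| 3 (primary endpoint) | yes | all deaths | yes, but not by type of event |
| 6a (all SAEs) | yes | yes | no |
| 6b (reason for seriousness) | no | yes | yes |
| 7 (drug-related SAEs) | yes | yes, if related | no |
| 8 (clinical grade 3 and 4) | yes | not if graded above 4 | no |

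No row of this table combines fatal adverse events, separately identified, with a split by arm. If fatal events were instead folded into grade 4, they would be in Table 8 but could not be told apart from survived events.

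**When the Table 8 comparison is distorted**

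In each arm, let S be the patients with any event of grade 3 or higher, and F those whose only such event was fatal. Patients left in the grade 3 and 4 rows number S − F. The difference between arms becomes

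(S₁ − S₂) − (F₁ − F₂).

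A true excess disappears when the two brackets are equal. It reverses when the excess in F is larger.

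Inputs: 520 enrolled (Structure and status of trial). The split of 260 per arm is an assumption, and so are all the rates below. The test is an uncorrected chi-squared, equivalent to z = (p₁ − p₂)/√(2p(1 − p)/260), where p is the pooled proportion. The last column counts patients with at least one event in any grade row. Table 8 has no clearly defined row for that total.

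| S, arm 1 v arm 2 | F, arm 1 v arm 2 | S − F, as left in Table 8 |
|---|---|---|
| 156 v 156 (p=1.00) | 52 v 52 | 104 v 104 (p=1.00) |
| 156 v 156 (p=1.00) | 65 v 52 | 91 v 104 (p=0.24) |
| 156 v 156 (p=1.00) | 78 v 52 | 78 v 104 (p=0.017) |
| 182 v 156 (p=0.017) | 78 v 52 | 104 v 104 (p=1.00) |
| 169 v 156 (p=0.24) | 57 v 52 | 112 v 104 (p=0.48) |

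For the third row: proportions 0.30 and 0.40, p = 182/520 = 0.35, standard error √(2 × 0.35 × 0.65/260) = 0.0418, z = 0.10/0.0418 = 2.39.

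**A second illustration, starting from mortality**

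Assume 104 (40%) v 130 (50%) deaths, each recorded as a fatal event, and a grade 3 or 4 event in 30% of survivors: 0.30 × 156 = 47 and 0.30 × 130 = 39.

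- Any grade 3 to 5: 104 + 47 = 151 (58%) v 130 + 39 = 169 (65%), a difference of 7 points.
- If 25% of those who died also had a separate grade 3 or 4 event: 26 + 47 = 73 (28%) v 32.5 + 39 = 71.5, about 72 (28%). This is a tie.
- If 50% did: 52 + 47 = 99 (38%) v 65 + 39 = 104 (40%). The direction is right and the difference is 2 points.

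Here the difference is masked or shrunk, not reversed.

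**The case against.** Three stronger readings are tempting, and the document supports none of them.

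- *Severe events are compared only as grades 3 and 4.* The one adverse event comparison for which the text names a test of patient numbers is any SAE by arm, with no grade limit. SAE episodes per patient are also compared informally with a quasi-Poisson model, and Table 7 has no grade limit either.
- *Fatal events drop out of the safety analysis.* Causing death is one of the seriousness criteria in Table 6b, so fatal events are SAEs. They count in Table 6a, and in Table 7 if related. They leave Table 8 only.
- *The arm with more fatal complications will appear to have fewer severe events.* This needs fatal events to be graded above 4, patients with no other grade 3 or 4 event, and a fatal-only excess larger than the true excess. The last row of the first illustration and both overlap cases of the second show no meaningful reversal.

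It can also be said that deaths by arm are fully analysed as the primary endpoint, and that keeping non-fatal toxicity apart from mortality is a defensible choice when mortality is this high. A grade 3-or-higher comparison would be dominated by death: in the second illustration deaths make up 104/151 = 69% and 130/169 = 77% of that total.

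These points limit the finding but do not remove it. All-cause mortality does not show which adverse events were fatal in which arm. Tables 6a and 7 count a fatal and a survived event alike. Separating non-fatal toxicity from death is sound only if the table says that it does so and the fatal part is shown by arm somewhere.

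**Conclusion.** The point holds as a gap in the planned tables. Table 8 has no row for fatal events, Table 6b pools the arms, and so no planned table shows fatal adverse events by arm. That much follows from the text alone.

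The possible distortion of the Table 8 comparison is conditional. It assumes that fatal events are graded above 4, and its size depends on how many patients have a fatal event as their only severe event, which the SAP does not give. Over the rates tried, the effect runs from none, through a masked difference (182 v 156 shown as 104 v 104), to a reversal (156 v 156 shown as 78 v 104). The primary analysis is not affected. The weight is minor to moderate.

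**What to change.** Do one of the following:

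1. Add a separate fatal (grade 5) row by arm to Table 8, and state in a footnote how an event ending in death is graded.
2. Show the death column of Table 6b by arm. This does not depend on how fatal events were graded.

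If a grade 3-or-higher patient total is added, place it beside the separate grade rows and not in their stead, because alone it would largely restate mortality.

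The cost is one row or one split column, plus a footnote. Table 6b already requires events that cause death to be identified, so no new classification should be needed, though the data forms are not shown. The downside is that fatal events appear in both the SAE and severity tables, and that a grade 3-or-higher total partly repeats the primary endpoint. The footnote can say both.

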## Structure and status of trial

The ACT HIV trial commenced recruitment on 25
^th^ May 2017. By April 29
^th^ 2021, the predefined sample size of 520 adults with TBM and HIV co-infection had been enrolled from four hospitals in Vietnam and Indonesia: the Hospital for Tropical Diseases (HTD) and Pham Ngoc Thach Hospital for Tuberculosis and Lung Disease (PNT) in Ho Chi Minh City, Vietnam, and Cipto Mangunkusumo Hospital and Persahabatan Hospital in Jakarta, Indonesia. Detailed enrolment criteria for ACT HIV, including consent and ethical approvals, are described in the published trial protocol
^
1
^.

Once enrolled, study participants were randomised to dexamethasone or placebo (a double-blinded allocation), with this intervention termed ‘study drug’. Randomisation was stratified by TBM MRC severity score and by hospital. Participants with MRC grade 1 TBM received a 6-week tapering course of study drug, whereas participants with MRC grades 2 or 3 received an 8-week tapering course of study drug. Study drug regimens are shown in
Table 1. Participants then underwent clinical assessments at baseline, at days 3, 7, 10, 14, 21, and 30, monthly until month 12, and then 3-monthly until 24 months. Baseline assessment included blood tests, chest X-ray, lumbar puncture, and brain imaging.

**Table 1. T1:** Study drug treatment regimen following randomisation.

	MRC Grade I Daily dexamethasone dose/route	MRC Grades II and III Daily dexamethasone dose/route
Week 1	0.3 mg/kg/24 hrs IV	0.4 mg/kg/24 hrs IV
Week 2	0.2 mg/kg/24 hrs IV	0.3 mg/kg/24 hrs IV
Week 3	0.1 mg/kg/24 hrs IV	0.2 mg/kg/24 hrs IV
Week 4	3mg/24 hrs oral	0.1 mg/kg/24 hrs IV
Week 5	2mg/24 hrs oral	4 mg/24 hrs oral
Week 6	1 mg/24 hrs oral	3 mg/24 hrs oral
Week 7	Stop	2 mg/24 hrs oral
Week 8		1 mg/24 hrs oral

IV=intravenous. MRC=Modified Research Council.

ACT HIV has numerous sub-studies, as described in the protocol
^
1
^. Key follow up outcomes include survival, disability, and severe adverse events; especially neurological events, events requiring corticosteroids, HIV-associated complications (malignancies, immune reconstitution inflammatory syndrome [IRIS]), and adverse events considered related to dexamethasone.

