## Trial endpoints

### Primary endpoint

The primary endpoint of the ACT HIV trial is death (from any cause) over the first 12 months after randomisation.

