## Primary endpoint

The primary endpoint of this trial is death over the first 12 months after randomisation. The primary analysis is a Cox proportional hazards regression model with treatment as the only covariate. Since TBM MRC severity grade at enrolment (I, II, or III) is an important risk factor for mortality and was used as stratification variable in the randomisation, we will additionally perform a secondary analysis with MRC grade added as stratum variable. The proportional hazards assumption will be formally tested based on scaled Schoenfeld residuals and visually assessed by a plot of the scaled Schoenfeld residuals versus transformed time. Deaths, by study drug arm, and the results of the analyses will be shown as per
Table 3 and
Table 4. 

**Table 3. T3:** Hazard ratio for death (from any cause) over the first 12 months after randomisation.

	No. of deaths		Hazard ratio (95% CI); p value	Test for proportional hazards
	Dexamethasone	Placebo		
All patients Corrected for modified MRC grade	XX/XX	XX/XX	X.XX (X.XX, X.XX) X.XX (X.XX, X.XX)	X.XX X.XX

The primary endpoint will be overall survival, i.e., time from randomisation to death, over the first 12 months of follow-up. This table reports the results from the Cox proportional hazards regression model. The primary effect measure will be the resulting hazard ratio comparing dexamethasone vs. placebo with a corresponding two-sided 95% confidence interval. In "All patients", treatment will be the only covariate. We will additionally report the hazard ratio if the modified MRC grade is included as stratum variable. The test for proportional hazards will use the Kaplan-Meier as time transformation. MRC=Modified Research Council.

**Table 4. T4:** Hazard ratios for death (from any cause) by sub-group over the first 12 months after randomisation.

	No. of deaths		Hazard ratio (95% CI); p value	Test for proportional hazards	p-value for heterogeneity *
	Dexamethasone	Placebo			
Modified MRC grade: - Grade I - Grade II - Grade III	XX/XX XX/XX XX/XX	XX/XX XX/XX XX/XX	X.XX (X.XX, X.XX) X.XX (X.XX, X.XX) X.XX (X.XX, X.XX)	X.XX X.XX X.XX	X.XX
Diagnostic category - Definite TBM - Probable TBM - Possible TBM - Not TBM	XX/XX XX/XX XX/XX XX/XX	XX/XX XX/XX XX/XX XX/XX	X.XX (X.XX, X.XX) X.XX (X.XX, X.XX) X.XX (X.XX, X.XX) X.XX (X.XX, X.XX)	X.XX X.XX X.XX X.XX	X.XX
*Leukotriene A4 hydrolase* - TT - CT - CC	XX/XX XX/XX XX/XX	XX/XX XX/XX XX/XX	X.XX (X.XX, X.XX) X.XX (X.XX, X.XX) X.XX (X.XX, X.XX)	X.XX X.XX X.XX	X.XX

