*LTA4H* genotype (CC/CT/TT), drug resistance pattern (MDR TB or rifampicin mono-resistant TB, isoniazid resistant non-MDR, no or other resistance), ART status at enrolment (ART naïve, ≤3 months of ART, >3 months of ART), and CD4 cell count at enrolment (<50, 51–100, 101–200, >200). We will estimate and report the treatment effect by fitting a separate Cox model per subgroup. We will additionally fit a Cox model that includes CD4 count at enrollment as a continuous variable via a restricted cubic spline with four knots and an interaction term with treatment arm.

Kaplan-Meier plots and explicit survival estimates at 3, 6, and 12 months of follow-up will be calculated for the full sample and in the subgroups defined above. We will compare the treatment arms via the absolute risk of death at 12 months (using a Wald-type test based on Kaplan-Meier estimates at 12 months and associated standard errors using Greenwood’s formula) and the restricted mean survival until 12 months (using the survRM2
^
12
^ package in R).

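### Table 6b pools the arms, so the plan never shows by arm which named serious adverse events were fatal, life-threatening or disabling

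*SAP article*

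**What the plan says.** In the SAP article, under Adverse events until 12 months, Table 6b is titled "Summary of serious adverse events, shown by reasons for which they were considered serious, not shown by study arm". Its rows are named events. Its columns are the seriousness criteria: death, threat to life, hospitalisation, disability, congenital anomaly and other important medical event. Its footnote defines the cell entries as patient counts with percentages, and N as all patients.

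The same section plans these comparisons by arm:

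- Patients with an SAE: "The number of patients with any serious adverse event will be summarised and compared between the two treatment arms based on the chi-squared test", with Fisher's exact test as the fallback for small expected counts. Table 6a carries this, including a row labelled "Serious adverse events of all types".
- SAE episodes per patient, "informally compared based on a quasi-Poisson regression model with treatment as the only covariate".
- Tables 7 to 10, covering drug-related SAEs, clinical grade 3 and 4 events, events that interrupt TB or antiretroviral treatment, and laboratory abnormalities. All have dexamethasone and placebo columns and a p-value column.

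Outside the safety section, the primary endpoint is all-cause: "The primary endpoint of the ACT HIV trial is death (from any cause) over the first 12 months after randomisation". Under Structure and status of trial, the key outcomes include "adverse events considered related to dexamethasone".

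**The concern.** In a placebo-controlled trial, a safety table says something about the drug only if it separates the arms. Table 6b alone links a named event to its consequence, and its caption rules out that separation. This is a stated choice about layout, not a detail left to the protocol.

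What is at stake is the interpretation of harm. A steroid given to immunosuppressed patients may plausibly reduce deaths from one cause and add deaths from another. An all-cause comparison shows the net effect. Seeing the components needs the fatal, life-threatening and disabling events named and counted in each arm. Randomisation makes such a table informative without anyone having to judge whether an event was drug-related, and pooling gives that up.

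**Working it through.** The SAP gives no figure to reproduce here. The check has two parts: what each display shows by arm, and a small illustration.

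**Displays compared**

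| Display | By arm? | Shows named SAE by reason for seriousness? |
|---|---|---|
| Tables 3 and 4, 12-month risk, restricted mean survival | Yes | No. Death from any cause |
| Modified Rankin scale at 12 months | Yes | No. Status at one time point, deaths scored 6, withdrawals and losses excluded |
| Table 6a | Yes | No. Patients and episodes, not split by criterion |
| Table 6b | **No** | **Yes** |
| Table 7 | Yes | No. Restricted to SAEs judged related |
| Table 8 | Yes | No. Grade 3 and grade 4 clinical events |
| Tables 9 and 10 | Yes | No. Treatment interruptions; laboratory abnormalities |

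No row has a yes in both columns. Table 8 is the nearest substitute for life-threatening events, but it falls short in two ways. It uses severity grade, whereas the Table 6b footnote requires immediate risk of death when the event occurred. Its separate grade 3 and grade 4 rows also leave out early events that were recorded only as one or the other; these go in a combined row.

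**Illustration (event counts are assumed)**

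Suppose one named SAE occurs in 20 patients per arm and is fatal in 16 patients overall.

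- Table 6a shows 20 v 20.
- Table 6b shows 16 under death, whatever the split between arms. The range of splits giving that same entry is:

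| Fatal, dexamethasone v placebo | Proportion of the 20 cases per arm | Table 6b entry |
|---|---|---|
| 16 v 0 | 80% v 0% | 16 |
| 12 v 4 | 60% v 20% | 16 |
| 8 v 8 | 40% v 40% | 16 |
| 4 v 12 | 20% v 60% | 16 |
| 0 v 16 | 0% v 80% | 16 |

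To scale the 12 v 4 case, the SAP gives 520 enrolled and mortality approaching 50% in people living with HIV. Assuming equal allocation, each arm has 520 / 2 = 260 patients and about 260 × 0.5 = 130 deaths. The difference is 12 − 4 = 8 deaths, and 8 / 130 = 6.2% of an arm's deaths.

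If dexamethasone also prevented 8 deaths from other causes, the totals would be 12 + 118 = 130 on dexamethasone and 4 + 126 = 130 on placebo. Tables 3 and 6a would then show equal counts and Table 6b would show 16. With arm columns, Table 6b would read 12/260 (4.6%) v 4/260 (1.5%) instead of 16/520 (3.1%).

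**The case against.** The strongest objection is that the worst outcomes are already compared by arm. A reader might infer from the Table 6b caption that the trial cannot show whether fatal, life-threatening or disabling events differ with dexamethasone. The document does not support that reading.

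- **Death** is the primary endpoint. The SAP states "Deaths, by study drug arm, and the results of the analyses will be shown as per" Tables 3 and 4, and adds "We will compare the treatment arms via the absolute risk of death at 12 months" and restricted mean survival.
- **Disability** at 12 months is compared on the modified Rankin scale with a proportional odds model.
- **Severity** is shown by arm in Table 8, so it would be wrong to say that any shift in severity without a shift in count is hidden.
- **Secondary endpoint 8** asks about any SAE by 12 months and is met by Table 6a. The key outcome of dexamethasone-related events is met by Table 7.

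The illustration also has limits. Its counts are invented and chosen to balance in Table 6a. Without an offset, the 8 extra deaths would enter Table 3. One might also divide 16 by 40 to get a pooled fatality of 40%, but Table 6b's footnote defines no such statistic: it counts patients out of all patients.

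All of this stands, and it sets the limits of the point. It does not remove it. All-cause death does not identify the cause, a Rankin score does not identify the event that led to disability, and grade 4 is not shown to be the same as life-threatening. It can also be said that Table 6b is an openly labelled descriptive supplement. That is true, but every other safety table in the section separates the arms and the SAP gives no reason for this exception.

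**Conclusion.** The point holds as a minor reporting weakness. The plan shows by arm how many patients died, how disabled survivors were and how many SAEs occurred. It does not show by arm which named SAEs were fatal, life-threatening or persistently disabling. A shift in these that leaves the totals unchanged would go unseen.

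No endpoint, test, analysis population or sample size is affected, and the primary result is unaffected. The finding rests on the table layouts alone. The illustration's size (8 deaths, about 6% of an arm's deaths) rests on assumed event counts, equal allocation and 50% mortality. It shows what the layout could hide and does not predict what the data contain.

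**What to change.** Drop the restriction in the Table 6b caption and put dexamethasone and placebo columns under each seriousness criterion. Report patient counts and percentages, with the patients randomised to each arm as denominator, and say so in the footnote. Keep the table descriptive with no p-values, which agrees with the SAP's rule that specific adverse events are not formally tested.

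The pooled table already requires each SAE to be coded by criterion, and arm is known at the final analysis, so no new data are needed. The cost is a wider table with many sparse cells. A footnote should warn against reading small differences as effects.
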